#### Participants’ characteristics and risk factors for hot flushes

Participants complete a *Demographics Questionnaire* upon enrolment into the trial, which collects demographic information and information on risk factors for hot flushes including:

i. ethnicity [5];

ii. menopausal status - staging system recommended by the Stages of Reproductive Ageing Workshop [65];

iii. smoking status [3];

iv. alcohol use [7,66];

v. physical activity [66];

vi. previous tubal ligation [67];

vii. history of depression [8];

viii. stress levels using the validated Perceived Stress Scale 4 [8,68];

ix. average weekly household income [3,68];

x. education level [68];

xi. BMI [6,7]; and

xii. information on previous use of acupuncture, including types of acupuncture used, date of last treatment, frequency of use, conditions treated, and perceived response to acupuncture

### Data storage and access

All hard copy information that contains personal information on participants or that can be identified is stored in a secure locked cabinet. Electronic data that contains personal information or that can be identified is password-protected on a secure server and can only be accessed by authorised researchers. Information will be retained for a minimum of fifteen years after publication of results.

### Sample size calculation

Sample size calculations are based on a two-sample *t*-test with 80% power and significance level at 5% for a two-sided test. We assumed conservatively that the mean hot flush score at baseline would be 14, the lowest possible entry score for the trial. Assuming a 50% relative reduction in the HF scores in the control group due to the placebo effect, which is the typical response reported in hot flush randomised controlled trials [69], we anticipate that women in the sham acupuncture group will have a mean hot flush score of 7 at EOT. To be clinically significant, we expect that women in the true intervention group to show at least 75% reduction in the total HF score from baseline, with a mean HF score of 3 at EOT. Based on these assumptions, 266 women (133 per trial group) will be needed to detect hot flush score difference of 4 (standard deviation (SD) = 11.6 [51]) between the two trial groups at EOT. This sample size is sufficient to detect a difference of 0.35 of 1 SD between the trial groups for the quality of life measures. Sample size was inflated to 360 women (180 per study group) to allow for attrition of 26% (experienced in the pilot study) at the measurement of the primary outcome at the EOT.

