## Discussion

Hot flushes are a common and potentially disabling symptom during the menopause. While HRT is an effective treatment, it does not suit all women either because of concerns over potentially serious adverse events, or because of relative contra-indications. Many women also prefer to use natural or complementary therapies where available. There is a paucity of effective and safe non-hormonal treatments for VMS. However, preliminary evidence suggests that acupuncture, a popular and safe treatment for a wide range of conditions, may be effective for VMS.

We are conducting a randomised sham-controlled trial on acupuncture for VMS, which builds on the results from our earlier pilot project during which feasibility of methods was demonstrated. This robustly designed study meets methodological benchmarks of adequate randomisation and allocation concealment procedures, blinding of outcome assessors and statisticians and utilising intention-to-treat analysis strategy. The trial method also allows for Traditional Chinese Medicine diagnosis in the eligibility criteria and a ‘dose’ of acupuncture reflecting clinical practice to ensure results are applicable to a broad range of health practitioners. The trial is appropriately powered to determine a clinically relevant treatment effect. Our results will determine the efficacy of acupuncture for treating VMS in postmenopausal women. In particular, we will assess the specific effect of insertion of the acupuncture needle and its contribution to the entire treatment effect.

Our results will inform women suffering with menopausal symptoms and both conventional and Traditional Chinese Medicine health care professionals on the potential role, if any, of acupuncture in the treatment of VMS. This will advance the field significantly and, if effective, will offer an important treatment option to reduce VMS and potentially improve quality of life in women at this important life stage. Future research may explore the optimal treatment regimen for acupuncture for VMS.

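### A 75% reduction from a baseline of 14 leaves 3.5, not 3: the 80% power holds for a difference of 4, but is about 69% at the 75% floor the plan calls clinically significant

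*Protocol article*

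**What the plan says.** The section Sample size calculation builds the target in steps. The test is a "two-sample *t*-test with 80% power and significance level at 5% for a two-sided test". The authors assume that "the mean hot flush score at baseline would be 14, the lowest possible entry score for the trial", and describe this as conservative. For the control arm they write "Assuming a 50% relative reduction in the HF scores in the control group due to the placebo effect", so that "women in the sham acupuncture group will have a mean hot flush score of 7 at EOT". For the active arm, the reduction is tied to clinical significance: "To be clinically significant, we expect that women in the true intervention group to show at least 75% reduction", which the same sentence equates with a mean of 3 ("at least 75% reduction in the total HF score from baseline, with a mean HF score of 3 at EOT").

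From these values the section concludes that "266 women (133 per trial group) will be needed to detect hot flush score difference of 4", with an SD of 11.6, and inflates the total to 360 (180 per group) for 26% attrition. The Discussion then states: "The trial is appropriately powered to determine a clinically relevant treatment effect".

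**The concern.** Two descriptions of one target sit in the same sentence and disagree. The percentage (75%) implies a mean of 3.5 and a difference from sham of 3.5. The printed mean (3) implies a 78.6% reduction and a difference of 4. The sample size rests on the second, while the label of clinical significance is attached to the first.

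Half a point looks like rounding, but the required sample size varies with the inverse square of the difference: (4/3.5)² = 1.306, so sizing for 3.5 needs about 31% more women than sizing for 4. A reader who takes the section and the Discussion together will assume 80% power at a 75% reduction. A non-significant result would then seem to count more strongly against an effect of that size than the design supports.

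**Working it through.** **Inputs** (all from Sample size calculation): baseline mean 14; sham reduction 50%; true acupuncture reduction at least 75%, printed mean 3; SD 11.6; two-sided α = 0.05; 133 evaluable per group; attrition 26%.

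**1. Reproduce the plan's own figure.**
- Standardised difference: 4 / 11.6 = 0.345.
- Normal approximation: n per group = 2 × (1.960 + 0.842)² × (11.6/4)² ≈ 132.0, rounded up to 133. The exact noncentral t solution is 132.99, also 133.
- Power with 133 per group: 80.0% (exact t), 80.3% (normal).
- Attrition: 266 / (1 − 0.26) = 359.5, rounded up to 360.

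The 266 and the 360 are therefore correct for a difference of 4.

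**2. Check the target.**
- Sham mean: 14 × 0.50 = 7.
- True acupuncture at a 75% reduction: 14 × 0.25 = 3.5. Difference: 7 − 3.5 = 3.5.
- Reduction implied by a mean of 3: (14 − 3) / 14 = 78.6%. Difference: 7 − 3 = 4.

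**3. Power at the 75% floor.**
- Standardised difference: 3.5 / 11.6 = 0.302.
- Normal approximation: 3.5 × √(133/2) / 11.6 = 2.461; 2.461 − 1.960 = 0.501; power 69.2%.
- Exact noncentral t: 68.8%. The type II error is 31% instead of 20%.

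**4. Size of the gap in women (for scale only).** Eighty per cent power at 3.5 needs 174 per group by the exact t, or 348 evaluable. With 26% attrition, 174 / 0.74 = 235.1, so 236 per group and 472 in all with equal allocation, against 360 planned.

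**5. How far the result depends on the assumptions.**

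| Change (133 per group, exact t) | Difference | Power |
|---|---|---|
| As stated: baseline mean 14, unadjusted | 3.5 | 69% |
| Baseline mean 15, same SD | 3.75 | 75% |
| Baseline mean 16, same SD | 4.0 | 80% |
| Baseline mean 17, same SD | 4.25 | 85% |
| Baseline adjustment, correlation 0.3 | 3.5 | 73% |
| Baseline adjustment, correlation 0.49 | 3.5 | 80% |
| Baseline adjustment, correlation 0.7 | 3.5 | 93% |

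The baseline rows use 25% of the baseline mean as the difference (75% minus 50%). The adjustment rows multiply the SD by √(1 − ρ²). Power of 80% returns when √(1 − ρ²) = 3.5/4 = 0.875, that is ρ = 0.484, or 0.49 when rounded up. The baseline means of 15 to 17 and all the correlations are assumptions; the documents give neither.

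**The case against.** The strongest reply is that the plan attaches its 80% to a difference of 4, prints the means of 7 and 3 openly, and delivers exactly that power. This stands. A reader might infer that the stated power is not delivered, or that the sample size calculation is wrong. The document supports neither reading: the formula, the 266 and the 360 all reproduce.

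A second reply is that a 78.6% reduction satisfies a requirement of at least 75%, so 3 may be read as a planning value above a floor. This also stands in part. It means that 69% is the power at the floor only, not across the whole range the plan would call clinically significant. It does not remove the mismatch, because the sentence presents 75% and a mean of 3 as one target, and the floor is what defines clinical significance.

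Third, 14 is the minimum entry score, so the actual baseline mean should be higher; at 16 with the same SD the difference is again 4. The direction is right, and it could cancel the shortfall. But the plan gives no expected baseline mean above 14, and the SD may rise with the mean.

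Fourth, the section Statistical methods foresees baseline as a covariate where appropriate, so the unadjusted t-test probably understates the power of the actual analysis. That is fair, but the sample size is explicitly based on the t-test and no correlation is given.

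Finally, the results will be reported with 95% confidence intervals. Those intervals, rather than planned power, will show whether a difference of 3.5 is excluded. This limits the harm from the misstatement. It does not make the sentence correct.

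**Conclusion.** The concern holds as an internal inconsistency in the stated target. A 75% reduction from 14 is a mean of 3.5 and a difference of 3.5 from sham. The design is powered at 80% for a difference of 4, which is a 78.6% reduction. At the 75% floor, power is about 69% (68.8% exact t, 69.2% normal).

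That figure assumes a baseline mean of exactly 14, SD 11.6, an unadjusted two-sample t-test, and 133 evaluable women per group after the full 26% attrition. If all 360 women were evaluable, power at 3.5 would be about 81%, but the plan itself expects the losses. The primary analysis, its estimate and its interval are unaffected. What needs correcting is the description of the target and the unqualified power claim in the Discussion.

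**What to change.** Correct the sentence in Sample size calculation in one of two ways:

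- restate the target as about a 79% reduction, with a mean of 3, a difference of 4 and 80% power; or
- keep the 75% reduction, give the mean as 3.5 and the difference as 3.5, and report about 69% unadjusted power with 266 evaluable women.

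Qualify the power claim in the Discussion to match the option chosen. It may be added that a baseline mean above 14 (16 gives a difference of 4 at the same SD), or adjustment for a baseline score with an assumed correlation of about 0.49, would restore 80% at a 75% reduction. Both should be labelled as assumptions.

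The cost is wording only; under the second option a stated figure becomes less favourable. The section Trial status reports that enrolment closed in March 2014, so no change to the sample size is proposed, and none is needed in the design or analysis.

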### Randomisation and allocation concealment

#### Sequence generation

Participants are randomly allocated to one of two trial groups: true acupuncture or sham acupuncture, using a computer-generated randomisation sequence, stratified by project acupuncturist using block sizes of either eight or twelve (with block sizes appearing in random order) within each stratum and an allocation ratio of 1:1. The research assistant responsible for allocating participants is not aware of the block sizes used. An independent researcher with no other involvement in the trial used this allocation sequence to create a password-protected electronic ‘spreadsheet’ which contains the covert allocation schedule. The principal investigator (MP) holds the randomisation schedule.

#### Implementation and allocation concealment

Upon confirmation of eligibility of women for the trial (that is, after completion of the baseline HFD and clinical confirmation of diagnosis of Kidney *Yin* deficiency), the unblinded research assistant (KN) uses the spreadsheet to randomly allocate participants to receive either real or sham acupuncture. The spreadsheet displays sequentially only the next treatment allocation.

The research assistant informs the relevant project acupuncturist of the allocation status by mobile phone text messaging, Email or fax, depending on the acupuncturist’s preference. Group allocation is indicated only by the list of acupuncture points for either real or sham acupuncture, to avoid unblinding should the participant inadvertently see the communication. As acupoints used for ‘needling’ in real and sham acupuncture groups are different, acupuncturists can easily identify group allocation from the list of points provided. This process can be cross-checked against the covert randomisation schedule code held by the principal investigator to ensure no corruption of the process has occurred. To prevent selection bias, all baseline information is collected prior to the acupuncturist being informed of the treatment allocation.

### Blinding

The research assistant responsible for randomisation (KN) and the project acupuncturists who deliver the treatment to the women are not blind to treatment allocation. Blinding of project acupuncturists is not possible because of the difference between real and sham acupuncture points used and the tactile difference between real and sham needling.

Participants and all other investigators are blinded, including the study statistician. As outcomes are self-assessed, outcome assessment is blinded. Data analysis will be performed where the treatment groups will be identified as Group A and B. The codes for the treatment groups will be revealed after the all outcome data collection is completed at six months.

### Safety

Prior to providing consent to participate, participants are informed of potential adverse events from acupuncture. Common adverse events include fainting, drowsiness, tiredness, temporary increase in symptoms, bruising and soreness. A practitioner guide to preventing and managing common adverse events is provided in the Practitioner Training Manual. Participants report adverse events either to the project acupuncturist delivering the intervention or the acupuncturist researcher. The project acupuncturist refers to the acupuncturist researcher in the event of ongoing or unresolved concerns. Serious adverse events (defined as potentially life-threatening, permanently incapacitating or resulting in hospitalisation) are notified to the study chief investigator (MP) and the Human Research Ethics Committee within 24 hours. Informed by the pilot project, it is anticipated that telephone advice from a general practitioner (MP/CE) and/or acupuncturist researcher (JS) will be adequate in most cases. If participants require additional medical advice, they are directed to their general practitioner. The expert acupuncturist (CX), who chairs the Chinese Medicine Board in Australia, is also available for advice.

Participants who score higher than 15 on the baseline depression and/or anxiety scales will be contacted by a general practitioner investigator (CE/MP) to be assessed for suicide risk and referred to relevant services as required.

Both the relevant project acupuncturist and the participant complete an Adverse Event Form should the need arise. The form records the dates and times that the event began and resolved; a description of the event; the intensity of the event (mild/moderate/severe); an assessment of the possible relationship to acupuncture, on a four-point Likert scale ranging from ‘unrelated’ to ‘definitely related’; the outcome on a five-point Likert scale ranging from ‘completely resolved’ to ‘persistent’; and whether the event was considered serious (potentially life-threatening, permanent incapacitating or resulting in hospitalisation).

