#### Treatment regimen

All participants receive ten thirty-minute treatments over eight weeks, twice weekly in the first two weeks and weekly thereafter. Treatments are provided at no cost to participants. All attempts are made to minimise missed sessions and limit breaks between sessions to two weeks or less.

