### Outcomes

Table 4 summarises the measures and the timing of their collection during the trial.

**Table 4 T4:** Summary of measures collected as part of the Acupause study

		**Run-in**	**Intervention**			**Follow-up**	
**Measure**	**Data collection instrument**	**Baseline**	**First treatment**^ **b** ^	**4 weeks**	**8 weeks/EOT**^ **c** ^	**3 months**	**6 months**
Demographic information, risk factor for VMS	Demographics Questionnaire	✓					
VMS frequency, severity and score	Seven-day day flush diary	✓		✓	✓^a^	✓	✓
Health-related Quality of life	Menopause-Specific Quality of life Questionnaire/MENQOL	✓		✓	✓	✓	✓
Depression and anxiety measures	Hospital Anxiety and Depression Scale/HADS	✓		✓	✓	✓	✓
Credibility and expectancy	Credibility Expectancy Questionnaire + additional question on binding		✓				

^a^Primary Outcome Measure. VMS, vasomotor symptoms.

^b^Immediately after the first treatment; ^c^End-of-treatment.

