#### Primary outcome measure

The primary outcome measure is the hot flush score at end-of-treatment (EOT). EOT hot flush score is calculated from the seven-day HFD which participants commence immediately upon completing their final treatment. These diaries have been used in multiple trials of interventions, and have been shown to be a consistent and reliable method of evaluating change in VMS [51].

Participants note daily in the diary the number and severity (mild, moderate, severe and very severe) of hot flushes experienced over a twenty-four hour period for seven days. The pilot study showed that it was feasible and acceptable for women to complete the diary over seven days with minimal missing data. The HFD will be used to determine three specific measurements: 1) hot flush frequency; 2) hot flush severity; and 3) a hot flush score comprising both frequency and severity. These scores are calculated as follows:

Hot flush frequency = total number of hot flushes reported/Number of days reported

Hot flush severity = (1 × number of mild hot flushes + 2 × number of moderate hot flushes + 3 × number of severe hot flushes + 4 × number of very severe hot flushes)/Number of hot flushes reported

Hot flush score = (1 × number of mild hot flushes + 2 × number of moderate hot flushes + 3 × number of severe hot flushes + 4 × number of very severe hot flushes)/Number of days reported

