#### Secondary outcome measures

i. Hot flush score at other time-points: the primary outcome measure is the hot flush score at the EOT; however, hot flush score will also be measured at four weeks to assess the intermediate effect of acupuncture and at three and six months to measure longer-term outcomes as recommended in the two recent systematic reviews [27,28].

ii. Health related quality of life: the *Menopause-Specific Quality of Life Questionnaire (MENQOL)* is a validated measure of quality of life and clinical change during the menopausal transition and is specific to women in the first eight years post menopause [59]. It consists of 29 items assessing four domains: VMS, physical symptoms, psychological symptoms, and urogenital/sexual symptoms.

iii. Anxiety and Depression: *Hospital Anxiety and Depression Scale (HADS)* is a validated widely-used 14-item self-report scale designed to briefly measure current anxiety and depressive symptoms in non-psychiatric hospital patients. It excludes somatic symptoms, therefore avoiding potential confounding factors [60]. The HADS comprises two independent seven-item subscales for anxiety and depression. Anxiety has been demonstrated to be a predictor of a high placebo response in menopause studies [61].

iv. Expectancy and beliefs about acupuncture: the *Credibility/Expectancy Questionnaire* is a validated, quick and easy-to-administer six-item scale for measuring treatment expectancy and rationale credibility for use in clinical outcome studies [62]. This questionnaire is administered once, immediately after the first treatment.

v. Success of blinding: as surveys to measure the success of blinding may enhance participants’ focus on this, we measure this aspect immediately after the first treatment [63]. There is currently no validated measure to assess blinding in acupuncture research. We will use the scale developed by Bang [64], which ranges from −1 (completely not blinded) to +1 (perfectly blinded).

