### Data collection

The Credibility/Expectancy Questionnaire, Case Report Form, TCM Diagnosis Form and Adverse Events Form are completed on paper copies. All other outcome measures, participant characteristics and risk factors for hot flushes are completed online using a survey management website (Survey Methods http://www.surveymethods.com), with paper copies available for those who prefer to use them. Online surveys have the advantage of minimising missing data if completion of survey questions is made mandatory prior to submitting the survey online. Range checks are also built into online surveys, and automated reminders are Emailed. The study acupuncturist and research assistant (CE and KN) oversee this data management. A reminder letter/Email is sent after two weeks, followed by a courtesy telephone call two weeks later by the research assistant should questionnaires not be returned. Details of treatment dates and follow-up are recorded in a custom-built password-protected database.

All paper-based data are entered into the same survey management website by staff blinded to group allocation at the University of Melbourne. Ten percent of all data entry will be audited by an independent investigator for quality assurance purposes.

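### The suicide-risk contact rule (depression or anxiety score above 15) is tied to the baseline HADS only, although the HADS is collected four more times

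*Protocol article*

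**What the plan says.** The Safety section of the protocol article prints a complete rule: "Participants who score higher than 15 on the baseline depression and/or anxiety scales will be contacted by a general practitioner investigator". The contact is for a suicide-risk assessment, with referral to services where required.

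The scales are the two subscales of the HADS. The section on secondary outcome measures describes it as a "self-report scale designed to briefly measure current anxiety and depressive symptoms". Table 4 (Outcomes), in the row "Hospital Anxiety and Depression Scale/HADS", schedules it at five points: baseline, 4 weeks, 8 weeks/end of treatment (EOT), 3 months and 6 months.

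The Safety section also gives general routes. "Participants report adverse events either to the project acupuncturist delivering the intervention or the acupuncturist researcher". Telephone advice from a general practitioner investigator or an acupuncturist researcher is expected to be enough in most cases, and women who need more medical advice are directed to their own general practitioner.

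**The concern.** The investigators judged that a score above 15 warrants a doctor's call about suicide risk. The scale measures current symptoms, so a low score at entry says little about a score months later. The article gives no reason why the same score should lead to a call at entry and to nothing at follow-up.

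A woman who first exceeds 15 at 3 or 6 months has told the trial so on its own questionnaire, and the printed rule asks nobody to contact her. Under Data collection, a woman who does not return her questionnaire receives a reminder and later a telephone call. One who returns it with a score above 15 has no contact triggered by that score.

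What is at stake is participant safety, not the efficacy result.

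**Working it through.** The article gives no figure to reproduce. The check sets the rule beside the schedule, then sizes the change.

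**1. Coverage of the rule.**

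| HADS collection (Table 4) | Score-triggered action (Safety) |
|---|---|
| Baseline | Contact, suicide-risk assessment, referral as required |
| 4 weeks | None stated |
| 8 weeks/EOT | None stated |
| 3 months | None stated |
| 6 months | None stated |

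The rule acts on 1 of 5 collections. The HADS or anxiety/depression levels also appear under secondary outcome measures, secondary analyses and abbreviations. None of these sets an action on a score. Data collection describes no alert on a score.

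**2. Who falls in the gap.** Women above 15 at baseline are contacted, assessed and referred as required. The gap is therefore mainly women who first exceed 15 later.

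**3. Other routes.** During treatment there is regular contact: "All participants receive ten thirty-minute treatments over eight weeks, twice weekly in the first two weeks and weekly thereafter". The primary outcome diary starts after the last session ("EOT hot flush score is calculated from the seven-day HFD which participants commence immediately upon completing their final treatment"), and no trial visit is described after that, although the 3-month and 6-month HADS are still to come. The reporting and advice routes are not said to stop at EOT, but they depend on the woman raising a problem.

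**4. Number of later forms.** With 360 women and full return, at most 4 × 360 = 1,440 forms carry no stated action, of which 2 × 360 = 720 fall at 3 and 6 months. These are forms, not women at risk. No lower bound follows from the 26% attrition in the sample size section. That figure is for the primary outcome at EOT, and losses at 3 and 6 months may be larger.

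**5. Forms the change could still reach.** Trial status says recruitment began in late 2011 and enrolment closed in March 2014. Assume 360 women enrolled evenly over 27 to 30 months and every form returned. Counting at the end of March 2014:
- 30 months, 3 and 6 months counted from randomisation: 360 × (1 + 2 + 3 + 6)/30 = 144 forms.
- 27 months, 3 and 6 months counted from EOT: 360 × (1 + 2 + 5 + 8)/27 = 213 forms.

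Lower return reduces both. If 1% to 5% of these forms exceed 15 (assumed), that is 0.01 × 144 = 1.4 to 0.05 × 213 = 10.7, or about 1 to 11 calls.

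**6. Overlap with the primary outcome.** A week-4 contact precedes the EOT diary. An EOT contact could fall within its seven days. On the same assumptions, 360/30 = 12 to 360/27 = 13 week-4 forms were outstanding, and 2 × 360/30 = 24 to 2 × 360/27 = 27 EOT forms.

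**7. Possible dilution of later psychological outcomes.** If one arm has 1 to 5 percentage points more women contacted and each gains 1 SD (both assumed), the arm means shift by 0.01 × 1 = 0.01 SD to 0.05 × 1 = 0.05 SD.

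**The case against.** The strongest reply is that nothing is contradicted. A check at entry and a repeated secondary outcome are compatible, and a journal article leaves much operational detail to a full protocol, which here was approved by four ethics committees. That has force against any claim that no wider rule exists, and no such claim is made. It has less force against the printed rule. The article gives the threshold, the caller, the action and the time point, and the time point is restrictive.

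A second reply is that women are not without help after baseline. This stands. A reader might infer that a woman who worsens later has no safety cover at all. The document does not support that: adverse event reporting, telephone advice and direction to her own general practitioner remain open. What is missing is a trigger from the score.

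A third reply concerns blinding. "Participants and all other investigators are blinded, including the study statistician", apart from the research assistant and the project acupuncturists. Yet one of the two general practitioner investigators, the principal investigator, holds the randomisation schedule (Sequence generation). The other, the acupuncturist researcher, may observe a treatment during site visits (Providers and standardisation of the intervention), and the points differ by arm. Their blinding may therefore be imperfect. This also stands. It argues for making calls without consulting allocation, not for making no calls.

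**Conclusion.** The point holds as a safety rule fixed too narrowly. It covers 1 of 5 scheduled HADS collections, and a woman who first exceeds 15 after baseline is outside it as printed. How many women that is cannot be computed from the document.

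Two stronger readings should be resisted. The count of later forms is not a measure of harm, and only its ceiling can be given. The gap also does not bias the efficacy comparison: sample size and the primary analysis method do not depend on it.

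The conclusion rests on the printed text alone. A full protocol that applies the threshold at every collection would reduce it to a correction of the article. The change is worth making because it is cheap, although late in the trial it can help only women with follow-up forms still to come.

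**What to change.** Delete *baseline* from the rule, so that a score above 15 on either scale at any scheduled HADS leads to the same contact, assessment and referral. In addition:

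- Score online forms on submission and paper forms on receipt. The survey already supports automation: "Range checks are also built into online surveys, and automated reminders are Emailed".
- Have the general practitioner investigators already named make the calls without consulting allocation. Prefer a caller known to be blinded where one is available, but let no call wait for one.
- Record post-randomisation contacts and referrals by arm, so that any imbalance can be reported.

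The cost is a one-sentence amendment, a score flag in the existing survey and a few calls, about 1 to 11 under the assumptions in step 5. The statistical downside is possible slight dilution of later HADS or MENQOL psychological contrasts, 0.01 to 0.05 SD under the assumptions in step 7. Contacts at week 4, and rarely at EOT during the diary week, could precede or overlap the primary outcome, but few such forms were still outstanding.
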